### Statistics

A Cox proportional hazards regression model will be used to describe the event, overall survival, where the variables MGMT, KPS, age, MRI findings of olfactory tract involvement and olfactory function will be used as the covariates. All models will be check for proportionality and the log likelihood will be used as the criteria for model selection. All statistical analysis and graphics will be conducted in R version 3.5.0 (Boston, MA).

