#### Sample size calculation and sampling strategy

The sample size was determined for a time-to-event analysis of Overall Survival (OS) using a Cox proportional hazards model. The calculation was based on the primary comparison between glioblastoma patients with hyposmia (defined as'cases'for the calculation) and those with normosmia (defined as'controls'). A hazard ratio (HR) of 0.43 for normosmia vs. hyposmia was used, a value derived from the multivariate analysis for OS in a specific subgroup of patients in the preceding pilot study [12]. As per the pre-specified statistical plan for this prospective trial, event rates over a two-year duration were prospectively defined at 47% for the hyposmia group and 53% for the normosmia group. With a significance level set at 5% and a statistical power of 80%, a total of 128 participants (64 glioblastoma patients and 64 healthy controls) is required to test this hypothesis. To control for key prognostic factors, patients are stratified after enrollment (at Visit 1) based on MGMT promoter methylation, KPS, age, extent of resection and MRI findings of olfactory tract infiltration. These variables, along with olfactory function, will be included as covariates in the final multivariate Cox proportional hazards model to adjust for potential confounding and assess the independent prognostic value of olfaction.

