### Perspective

This prospective, multicenter observational study aims to clarify the prognostic significance and underlying mechanisms of olfactory dysfunction in newly diagnosed glioblastoma. Previous retrospective data have suggested an association between impaired olfaction and reduced survival in glioblastoma patients [12], but those findings were limited by potential confounders and lacked longitudinal follow-up. This study was designed to overcome these limitations by integrating rigorous stratification, serial olfactory testing, multimodal imaging, neurocognitive assessments, and molecular profiling.

The primary objective is to determine whether olfactory dysfunction independently predicts overall survival when accounting for established prognostic factors such as MGMT promoter methylation, KPS, age, and extent of resection. In parallel, two mechanistic hypotheses are tested: (1) direct tumor invasion of olfactory-related structures, and (2) neurotoxicity resulting from radiotherapy or chemotherapy. The aim is to prove that an olfactory dysfunction in glioblastoma is intrinsic to the disease and is not caused by radiochemotherapy or local tumor infiltration in the olfactory tract.

To assess structural involvement, high-resolution coronal T2-weighted MRI and DTI are employed to detect infiltration of primary and secondary olfactory regions. Metabolic activity in these areas is further evaluated using FET PET in clinically indicated cases. These imaging data are assessed independently by two neuroradiologists to ensure objective interpretation.

To investigate treatment-related neurotoxicity, olfactory function is longitudinally monitored over two years using both identification and threshold components of the Sniffin’ Sticks test. These data are complemented by repeated neurocognitive testing, and quality of life assessments, allowing for correlation between sensory decline, cognitive function, and psychosocial burden.

The study incorporates matched healthy controls to provide normative data and differentiate disease-specific patterns from age-related olfactory decline. Additionally, tumor genome sequencing and biobanking enable exploratory analyses of molecular correlates of hyposmia and clinical outcome.

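### The Statistics section leaves extent of resection out of the overall-survival Cox model, while the sample-size section puts it in, so the main model is not uniquely defined

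*Protocol article*

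**What the plan says.** Three places in the protocol article bear on the adjustment set for overall survival.

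- **Sample size calculation and sampling strategy.** The purpose is stated first: "To control for key prognostic factors, patients are stratified after enrollment (at Visit 1"). The factors are then listed: "based on MGMT promoter methylation, KPS, age, extent of resection and MRI findings of olfactory tract infiltration". The section goes on: "These variables, along with olfactory function, will be included as covariates in the final multivariate Cox proportional hazards model". That makes six terms, one of which is extent of resection.
- **Statistics.** This section describes a single Cox model for overall survival, "where the variables MGMT, KPS, age, MRI findings of olfactory tract involvement and olfactory function will be used as the covariates". That makes five terms, and extent of resection is not among them.
- **Perspective (main text).** The primary objective is to establish whether olfactory dysfunction predicts overall survival independently, "when accounting for established prognostic factors such as MGMT promoter methylation, KPS, age, and extent of resection".

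The abstract's Methods paragraph and the Study cohort section also name extent of resection as a stratification factor. Nothing in the article explains why the Statistics list is shorter.

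**The concern.** Olfactory status is observed, not randomised, so the claim that it is an independent prognostic marker rests on the adjustment set. The Introduction says the preceding study was criticised because prognostic factors were not evenly spread between the olfactory groups, and this study is offered as the remedy. Two different closed covariate lists for the same endpoint weaken that remedy in two ways. A reader cannot tell which hazard ratio is the main result, and the analyst could choose between two written models after seeing the data. If the shorter list is the one applied, the analysis also falls short of the stated primary objective, which names extent of resection.

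**Working it through.** **Step 1. Set the lists side by side.**

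| Term | Sample-size section (final Cox model) | Statistics section | Primary objective (Perspective) |
|---|---|---|---|
| Olfactory function | yes | yes | yes (the marker) |
| MGMT promoter methylation | yes | yes | yes |
| KPS | yes | yes | yes |
| Age | yes | yes | yes |
| MRI olfactory tract involvement | yes | yes | not named |
| Extent of resection | **yes** | **no** | **yes** |
| Number of terms | 6 | 5 | (examples only) |

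The sample-size and Statistics lists differ in one term only. The objective is worded as a list of examples, so not naming the MRI term there is no conflict. It does name extent of resection.

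**Step 2. Could another part of the plan explain the omission?** Stratification could, if factors balanced by stratification were deliberately left out of the model. But MGMT, KPS, age and MRI findings are also stratification factors, and the Statistics section keeps all four. Model selection by log likelihood does not explain it either: a selection rule gives no reason to leave one candidate off the list beforehand.

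**Step 3. Size of the bias if the five-term model is used.** The documents give neither the effect of resection on survival nor its distribution by olfactory group, so these inputs are assumptions:

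- hazard ratio for more complete resection: 0.7 to 0.5, i.e. |β| = ln(1/0.7) = 0.357 to ln(1/0.5) = 0.693
- difference between olfactory groups in the share with more complete resection: 0, or 0.10 to 0.25, with less complete resection in the hyposmic group

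Approximate factor on the hyposmia hazard ratio = exp(|β| × imbalance):

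- exact balance: exp(0) = 1.00
- low end: exp(0.357 × 0.10) = 1.04
- high end: exp(0.693 × 0.25) = 1.19

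The plan states its effect the other way round: "A hazard ratio (HR) of 0.43 for normosmia vs. hyposmia was used". On that scale 0.43 would become 0.43/1.04 = 0.41 at the low end and 0.43/1.19 = 0.36 at the high end, further from 1. If the imbalance ran the other way, the shift would be towards 1.

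Cross-check with the ratio of average hazards. With g the hazard ratio for less complete resection, and p1, p0 its share in the hyposmic and normosmic groups, the factor is (1 + p1(g − 1))/(1 + p0(g − 1)):

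- g = 1.43, 55% vs 45%: 1.236/1.193 = 1.04
- g = 2.0, 62.5% vs 37.5%: 1.625/1.375 = 1.18

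The two approximations agree.

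**Step 4. Compare with the precision available.** The planned two-year event rates are 47% and 53%, a mean of 50% if the groups are equal, so 64 patients give about 64 × 0.50 = 32 events. The standard error of the log hazard ratio is then about 2/√32 = 0.35. The assumed bias on the log scale is 0.357 × 0.10 = 0.036 to 0.693 × 0.25 = 0.17, or about 0.1 to 0.5 of a standard error. The planned effect is |ln 0.43| = 0.84.

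**Step 5. Cost of the sixth term.** Counting one parameter per term, events per parameter go from 32/5 = 6.4 to 32/6 = 5.3.

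**The case against.** The strongest reply is that this is a drafting slip. The sample-size section is the more specific text: it speaks of the final multivariate model and gives its purpose. The Statistics section does not call its model primary or final. Extent of resection appears everywhere else that the prognostic factors are listed. This stands as far as it goes. A reader might infer that the reported hazard ratio will be unadjusted for resection, but the documents do not support that. It follows only if the Statistics list is the one applied, and the article does not say which list governs.

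A second reply is that the design itself controls for resection. The Study cohort section says that stratification balances the olfactory groups on it and that patients who cannot be assigned are excluded. This also has force: under exact balance the confounding is about nil, so one cannot say that the omission leaves in place the confounding the study was meant to remove, or that the two models must give different answers. It does not settle the matter, because the sample-size section asks for covariate adjustment on top of stratification, and the Statistics section itself adjusts for the other stratification factors.

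A third reply is that the bias is small against the sampling error. Under the assumptions above that is correct: at most about half a standard error. But the shift is systematic and would not shrink with more patients.

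**Conclusion.** The contradiction is plain in the text and rests on no assumption: two closed covariate lists for the overall-survival Cox model differ by extent of resection, and the primary objective sides with the longer one. The main model is therefore not uniquely defined and must be reconciled before outcomes are analysed.

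The numerical consequence is conditional. It needs the shorter list to be applied and an imbalance in resection to remain after stratification. Under exact balance the bias is about nil. Under an assumed resection hazard ratio of 0.5 to 0.7 and a 10 to 25 point imbalance, it is a factor of about 1.04 to 1.19 on the hyposmia hazard ratio, with a direction that depends on which group has the less complete resections. None of these inputs is in the documents.

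**What to change.** In the Statistics section, add extent of resection to the covariate list, so that the overall-survival model contains olfactory function, MGMT promoter methylation, KPS, age, extent of resection and MRI olfactory tract involvement as the protocol defines it. State that this is the primary model. The list then matches the sample-size section and serves the primary objective. The Perspective wording can stay as it is, since it gives examples and does not specify a model.

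The cost is one line of text and one model parameter. Extent of resection is already needed for stratification, so no new data are collected and no stated figure changes. The price is in precision: about 5.3 instead of 6.4 events per parameter at roughly 32 events, a cost the sample-size section has already accepted by listing six terms. Enrolment is planned to run to December 2026 and follow-up to December 2028, so the correction can be made before the final analysis. Which MRI should define tract involvement is a separate question and is not part of this change.

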In a previous study, we demonstrated that patients with glioblastoma are significantly more prone to olfactory dysfunction than a control group of patients with non-tumorous neurological diseases not primarily associated with smell impairment [12]. The study demonstrated the prognostic relevance of an olfactory dysfunction in glioblastoma patients regardless of the olfactory tract affection by the tumor. We studied 122 patients (73 glioblastoma patients and 49 controls). All were tested at various time points using the Sniffin Sticks screening test—a 12-odor test where participants identify each odor from four predefined options. Normosmia was defined as a Sniffin Sticks score (SSC) of 9.9 or higher [10]. Patients scoring below 10 were classified as the hyposmia group (HG), while those scoring 10 or higher were classified as the normosmia group (NG) [12]. After the initial examination, 34 glioblastoma patients were assigned to the HG and 39 to the NG. O6-Methylguanine-DNA Methyltransferase (MGMT) promoter methylation, age, sex, Karnofsky performance status (KPS), tumor histology, and extent of resection did not differ significantly between the two groups. Glioblastoma patients scored significantly lower on the smell test than controls (mean SSC 8.9 vs. 9.9, *p* = 0.003). Even patients tested before chemotherapy or radiotherapy onset performed worse than controls (mean SSC 8.2 vs. 9.9, *p* = 0.001). MRI was used to determine if tumor growth affected primary olfactory centers (ethmoid bone, olfactory groove, or temporomesial structures like the posterior orbitofrontal cortex, uncus, anterior parahippocampal gyrus, entorhinal area, insula, or amygdala). The median overall survival (OS) of the cohort was 28.1 months, and the median progression-free survival (PFS) was 14 months. Patients in the HG had worse OS (20.9 vs. 40.6 months, *p* = 0.035) and PFS (9 vs. 19 months, *p* = 0.022) compared to NG.

In our previous study, longitudinal analysis was hampered by limited re-examinations during follow-up (n = 32). Only some patients were assessed before chemoradiotherapy (n = 15), restricting our ability to evaluate neurotoxicity from radio- and chemotherapy. Additionally, the HG was older, had lower MGMT promoter methylation rates, and a lower KPS than the normosmia group—differences that, though not statistically significant, are crucial in ensuring that the groups were not distributed exactly equally, which led to criticism from readership.

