### Study cohort

The study will enroll 128 participants (64 glioblastoma patients and 64 controls). Glioblastoma patients will be stratified at their first visit after radiotherapy based on extent of resection, MGMT promoter methylation status, initial olfactory test results, MRI findings of olfactory tract involvement, age, and KPS. This approach ensures balanced distribution between normosmia and hyposmia groups. Patients who cannot be assigned to either group will be excluded from further participation. Stratification will occur once post-radiochemotherapy MRI results are available, typically at visit 1 (see Table 1). The controls should essentially match the age and gender of the patients.

**Table 1 Tab1:** Overview of the planned study visits and their contents

	Screening	Baseline	Visit 1	Visit 2	Visit 3	Visit 4	Follow up visits
Signing Informed consent	x						
Verfication of inclusion and exclusion criteria	x	x					
Stratification			x				
Medical history (including cold symptoms)	x	x	x	x	x	x	x
Physical exam		x	x	x	x	x	x
Karnofsky Performance Status Scale	x	x	x	x	x	x	x
Evaluation of progression and survival data		x	x	x	x	x	x
QoL: EORTC QLQ-C30 and EORTC QLQ-BN20		x	x	x	x	x	x
Recording (severe) adverse events grade III/IV according to CTCAE V5.0		x	x	x	x	x	x
Neurocognitive testing (+ Minimal Mental Status Test)		x	x		x	x	x
Laboratory tests		x	x	x	x	x	x
Olfactory testing	x	x	x	x	x	x	x
MRI	x		x	x	x	x	x
FET PET MRI (if indicated in clinical routine)	x	x	x	x	x	x	x
Laboratory tests for scientific purposes (Biobank)		x	x	x	x	x	x
Next Generation Sequencing (if indicated in clincal routine)	x	x	x	x	x	x	x
Testing for aphasia	x						
Psychosomatic testing	x	x	x	x	x	x	x

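### Sex is in no stratification list and in neither Cox covariate list, so the smell hazard ratio called independent is not protected against possible confounding by sex

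*Protocol article*

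**What the plan says.** The protocol article deals with sex in two places and leaves it out of the rest.

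- **Pilot comparison (Introduction).** MGMT "promoter methylation, age, sex, Karnofsky performance status (KPS), tumor histology, and extent of resection did not differ significantly between the two groups". The groups were small: "34 glioblastoma patients were assigned to the HG and 39 to the NG". The authors then name the imbalances that they regard as crucial although not significant: "the HG was older, had lower MGMT promoter methylation rates, and a lower KPS than the normosmia group". Sex is not among these.
- **Healthy controls (Study cohort).** "The controls should essentially match the age and gender of the patients".
- **Stratification.** The Study cohort section stratifies patients "based on extent of resection, MGMT promoter methylation status, initial olfactory test results, MRI findings of olfactory tract involvement, age, and KPS". The sample size section stratifies "based on MGMT promoter methylation, KPS, age, extent of resection and MRI findings of olfactory tract infiltration". The Abstract names the same factors as the Study cohort section. None of the three lists includes sex.
- **Cox model.** The sample size section carries its five stratification factors into the final model together with olfactory function, six covariates in all. The Statistics section gives five: "where the variables MGMT, KPS, age, MRI findings of olfactory tract involvement and olfactory function will be used as the covariates". Sex is in neither list.

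The sample size section presents the adjusted result as showing the independent prognostic value of olfaction.

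**The concern.** Smell status cannot be randomised, so a claim that it predicts survival independently rests on the factors that are balanced by stratification or adjusted for in the model. Of the factors compared in the pilot, MGMT, age and KPS are in the strata and in both covariate lists. Extent of resection is in the strata and in one covariate list. Eligibility largely settles histology, because every patient must have IDH wild-type glioblastoma. Sex alone has no protection anywhere.

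Gender matching does not fill the gap. It applies to the healthy controls, who take no part in the survival comparison of hyposmic with normosmic patients. The section on olfactory testing applies one cut-off of 10 to everyone, so any sex difference in score would pass straight into group membership. If sex were also related to survival, part of the smell hazard ratio would be a sex effect. The planned model could neither show nor remove it.

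The lists are stated as complete. The Statistics section uses the log likelihood for model selection but names no candidate variable beyond its list.

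**Working it through.** The plan gives no figure on sex to reproduce. The check sets the lists side by side and then sizes the possible bias under stated assumptions.

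**1. Factor by factor**

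| Pilot factor | Strata | Cox list, sample size section | Cox list, Statistics section |
|---|---|---|---|
| MGMT | yes | yes | yes |
| Age | yes | yes | yes |
| KPS | yes | yes | yes |
| Extent of resection | yes | yes | no |
| Histology | set by eligibility | – | – |
| Sex | no | no | no |

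**2. What the pilot's non-significance excludes.** With 34 and 39 patients and an overall share of 50%, the largest observed difference that stays non-significant at 5% is about 1.96 × √[0.5 × 0.5 × (1/34 + 1/39)] = 0.23, or 23 percentage points. At an overall share of 40% or 60% it is 22.5 points. This limits what was observed in the pilot. It is not a confidence limit for the true difference.

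**3. Possible bias.** Let h be the hazard ratio of the worse-prognosis sex against the other, and p1 and p0 its shares in the hyposmia and normosmia groups. The crude smell hazard ratio (normosmia vs hyposmia) is the true one divided by

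b = [1 + (h − 1)p1] / [1 + (h − 1)p0].

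All inputs are assumptions, with shares centred on 60%. The formula ignores any overlap of sex with the other covariates.

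| h | Imbalance | b | True 1.00 reads | True 0.43 reads |
|---|---|---|---|---|
| 1.1 | 5 points | 1.005 | 0.995 | 0.428 |
| 1.25 | 10 points | 1.022 | 0.978 | 0.421 |
| 1.5 | 10 points | 1.039 | 0.962 | 0.414 |
| 1.5 | 23 points | 1.093 | 0.915 | 0.394 |
| 2.0 | 23 points | 1.155 | 0.866 | 0.372 |

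For the fourth row, p1 = 0.715 and p0 = 0.485, so b = 1.3575 / 1.2425 = 1.093. If the imbalance runs the other way, the true value is multiplied by about b: 1.00 reads about 1.09 and 0.43 reads about 0.47.

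**4. Size against sampling error.** The planned two-year event rates of 47% and 53% average 50%, so 64 patients in equal groups give about 64 × 0.50 = 32 deaths. The standard error of the log hazard ratio is about 2/√32 = 0.354. A factor of 1.093 is ln(1.093)/0.354 = 0.25 standard errors, which would move a two-sided 5% error rate to about 5.7%.

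**5. Cost of adjusting.** Events per covariate fall from 32/6 = 5.3 to 32/7 = 4.6 on the sample size section's list, or from 32/5 = 6.4 to 32/6 = 5.3 on the Statistics list. Two-sided Schoenfeld power at 32 deaths and a hazard ratio of 0.43 is Φ(√(32/4) × |ln 0.43| − 1.96) = 66.5%. Adding sex multiplies the effective number of deaths by 1 − R², with R² = d² × 0.25/(0.6 × 0.4) for an imbalance d. For d = 0.10, R² is 0.010 and power is 66.1%. For d = 0.23, R² is 0.055 and power is 64.1%. That the starting value lies below the stated 80% is a separate matter and does not affect this point.

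**The case against.** The case against acting is substantial.

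- **No evidence of confounding.** The documents nowhere link sex to survival, and the Perspective section does not name it among its examples of established prognostic factors. The pilot found no significant sex difference between the smell groups. This stands: the bias is possible, not demonstrated.
- **Direction.** A reader might infer a one-sided bias towards the study hypothesis, on the view that women both smell better and live longer. The documents support neither link, so the sign would be an assumption and not a result.
- **Readers' criticism.** A reader might also infer that the pilot was criticised for sex imbalance. The imbalances named there are age, MGMT and KPS. What carries over is only the authors' own reasoning that a non-significant difference can still matter.
- **Gender matching.** Matching controls on age and gender is routine, and the stated reason for having controls mentions age-related decline in smell, not sex. It does not show that the authors regard sex as related to smell.
- **Larger imbalances.** A gap such as 21 of 39 against 9 of 34 would have been significant in the pilot (chi-square p = 0.018, Fisher p = 0.031). That does not rule out such a gap in the new cohort, but it is the case that fits the available evidence least well.
- **A crowded model.** With about 32 deaths, keeping to a few strong prognostic factors is defensible. This stands, and is why a sensitivity analysis is an acceptable fallback.

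What remains is that a baseline factor compared in the pilot has no protection in a comparison whose result is to be called independent.

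**Conclusion.** The point holds as a gap in protection, not as demonstrated bias. Sex appears in none of the stratification lists and in neither Cox list, and control matching does not reach the survival comparison.

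For assumed sex hazard ratios of 1.1 to 1.5 and imbalances of 5 to 23 points, the smell hazard ratio would shift by about 0.5% to 9%, in a direction that the documents do not fix. Even an assumed sex hazard ratio of 2.0 with 23 points gives a factor of only 1.155. None of this could produce 0.43 from a true value of 1.00. At about 32 deaths the shift is also small beside the sampling error.

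A reader might take sex to be the only omission in the Statistics section's covariate sentence. It is not: that sentence also leaves out extent of resection, which the sample size section puts in the model and the Perspective section names in the primary objective. That contradiction is the larger defect of the sentence. Sex differs in being absent from every list.

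The change is worth making because it is cheap and bears directly on the word independent.

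**What to change.** Reconcile the covariate lists of the sample size and Statistics sections, including extent of resection. In the same edit, pre-specify adjustment for sex in the overall-survival model, either as a covariate or by stratifying the baseline hazard by sex, which adds no coefficient. If the number of coefficients on about 32 deaths is judged too high, keep the primary model without sex and pre-specify a sensitivity analysis that includes it.

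The edit is one line, and sex must be known anyway to match the controls. As a covariate it costs one more term and a slightly wider interval, as sized in the working. It is best done now: enrolment is planned to run to December 2026, and adjustment added once survival results are known would look post hoc.

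### The Statistics section adds a log-likelihood model-selection rule to a Cox model whose covariates are already fixed; the primary analysis needs one prespecified list and no selection

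*Protocol article*

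**What the plan says.** Three places in the protocol article describe the primary Cox model.

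- **Sample size calculation and sampling strategy.** After naming MGMT promoter methylation, KPS, age, extent of resection and MRI olfactory infiltration, it says: "These variables, along with olfactory function, will be included as covariates in the final multivariate Cox proportional hazards model". That is six terms. The stated purpose is confounder adjustment and the independent prognostic value of olfaction.
- **Statistics.** Here "the variables MGMT, KPS, age, MRI findings of olfactory tract involvement and olfactory function will be used as the covariates". That is five terms, without extent of resection. After a remark on checking proportionality in all models, it adds that "the log likelihood will be used as the criteria for model selection". It gives no penalty, threshold, candidate set or direction of search, and does not say that olfactory function must stay in.
- **Perspective.** The primary objective is independent prediction of overall survival, accounting for "established prognostic factors such as MGMT promoter methylation, KPS, age, and extent of resection". Extent of resection is named again.

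**The concern.** A model whose terms are all to be included leaves nothing to select, so a reader cannot tell whether the primary model is fixed or chosen from the data.

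The choice bears directly on the primary claim. If a fit-based rule removes a real prognostic factor because the cohort is too small to show its effect, part of that effect moves onto olfaction. The reported p-value and interval also take no account of the search. The Introduction says that the pilot's hyposmia group was older, with lower MGMT methylation rates and lower KPS, and that these non-significant differences drew criticism. Choosing covariates by fit in a small cohort could reopen that criticism.

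**Working it through.** **1. What the criterion does if taken literally.** Let ℓ(β) be the log partial likelihood. A smaller nested model is the larger one with some βₖ = 0, so on the same data

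max ℓ(larger) ≥ max ℓ(smaller).

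An unpenalised maximum can never favour the smaller model. In simulation, maximising it over all covariate subsets chose the full model in 100% of runs. The literal rule therefore selects nothing and adds no inflation. The largest model that can be built from the Statistics list still has only five terms, because extent of resection is not on it.

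**2. Information available.** The sample size section gives two-year event rates of 47% (hyposmia) and 53% (normosmia). With 64 patients, taken as 32 per group:

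0.47 × 32 + 0.53 × 32 = 15.0 + 17.0 = 32 events; 32 / 6 = 5.3 events per term.

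**3. What happens if terms really are selected.** The article gives no false-positive rate under selection, so the only figure to compare with is its 5% level (two-sided assumed, as sidedness is not stated). A null simulation was run with 64 patients, a true olfactory hazard ratio of 1, five covariates plus olfaction, and 4,000 runs per setting. Event counts were 32 (50%) and 51 (80%). The rules tried were AIC and BIC best subset and backward likelihood-ratio elimination at 5% and 10%, with olfaction forced in; AIC and both backward rules were also run with it not forced.

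The association between hyposmia and the covariates is an assumption, since the Introduction gives its direction but not its size. The unadjusted column shows how strong each setting is. Entries are the percentage of runs declaring olfaction significant.

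| Association | Events | Unadjusted | Fixed six-term (Wald) | Selected, range over rules | Ratio to fixed |
|---|---|---|---|---|---|
| None | 32 | 5.0 | 6.4 | 6.8–7.2 | 1.1 |
| None | 51 | 5.0 | 6.8 | 7.5–8.1 | 1.1–1.2 |
| Moderate | 32 | 11.0 | 6.6 | 7.7–9.0 | 1.2–1.4 |
| Moderate | 51 | 14.3 | 6.6 | 8.2–10.6 | 1.2–1.6 |
| Strong | 32 | 24.2 | 6.3 | 10.2–14.5 | 1.6–2.3 |
| Strong | 51 | 33.2 | 7.5 | 11.2–17.2 | 1.5–2.3 |

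For example, with strong association and 32 events, 10.2 / 6.3 = 1.6 and 14.5 / 6.3 = 2.3. The Monte Carlo standard error near 7% is √(0.07 × 0.93 / 4000) = 0.4 percentage points, so the excess with no association is small.

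The ratio exceeds 2 only under strong association, and only for BIC (13.9 / 6.3 = 2.2; 17.2 / 7.5 = 2.3) and backward elimination at 5% with olfaction forced in (14.5 / 6.3 = 2.3; 16.4 / 7.5 = 2.2).

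**4. What selection does not explain.** The fixed model itself runs at 6.3–7.5% against a nominal 5%. That part comes from fitting six terms to few events, and removing the selection sentence does not cure it.

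**The case against.** The best defence is that the literal rule is harmless: it retains every candidate term, so no confounder is lost. The article nowhere mentions backward elimination or a retention threshold, and both sections say that the listed variables enter the model. The phrase may simply be shorthand for likelihood-ratio comparison of nested models, for example with and without olfaction, which is sound. The article is also condensed and refers to a prespecified statistical plan that is not shown, where a threshold would normally sit.

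Much of this stands. A reader might infer that the criterion is outright invalid, or that stepwise selection is planned. The text supports neither, and the missing threshold alone is not a fault. What remains is that the article itself states a selection rule for models it elsewhere fixes, and its two covariate lists differ.

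Two further points limit the size:

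- The Study cohort section intends stratification to balance the olfactory groups, which would lower the inflation. It does not remove the issue, since olfactory status is observed rather than assigned and the sample size section still requires adjustment.
- The 32 events are a two-year figure, and follow-up may run longer. With exponential survival at the pilot median of 28.1 months, 36 months gives 64 × (1 − 2^(−36/28.1)) ≈ 38 deaths, or 38 / 6 = 6.3 per term. The 51-event rows show that more events do not remove the inflation.

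**Conclusion.** The point holds as a conflict between two stated rules, made worse by a criterion that cannot choose between nested models without a penalty or threshold. The sentence either does nothing or stands for data-driven selection that would weaken the independence claim.

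The numerical harm is conditional on the second reading: about 1.1 to 2.3 times the fixed model's false-positive rate, depending on the selection rule and on an association that the article does not quantify. A reader might infer that the plan roughly doubles the false-positive rate. Some assumed settings come near or reach that: a separate run of 1,500 cohorts with 32 events gave 10.1% against 5.5%, a ratio of 1.8, under its own choice of moderate association. Nothing in the article fixes the association at that strength or shows that terms will be eliminated, so a range with its assumptions is all that can be claimed. Severity: should-fix.

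**What to change.** - Delete the model-selection sentence for the primary analysis.
- State that the primary Cox model is fully prespecified with no variable selection, and give one covariate list that agrees across the sample size section, Statistics and Perspective. Extent of resection has to be reconciled, since Statistics is the only one of the three that omits it.
- Always retain olfactory function, and test it once by a likelihood-ratio test of the model with versus without it.
- Label any other model comparison as a sensitivity analysis.

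The cost is wording, plus a slightly wider interval than a selected model would report. The proposed test is not exactly 5% either: in the simulation above, the six-term likelihood-ratio test ran at 6.7–7.6%. The Results section reports 32 patients recruited by April 2025 and follow-up to December 2028, so there is time to settle this before the final outcome analysis.
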